### Data management

The data collection process will be conducted as per the defined protocol and standard operating procedures approved by the committee, to ensure genuine and good quality data. The patients will be given a study explanation session and after giving their consent, will be randomized and have their baseline data documented. After consultation, they will be informed about their follow-up visiting schedules. Patients with RA are usually given a follow-up appointment after 3 months. In addition, they are reminded about their visits via text reminders and followed by telephone calls if absent on the day of the appointment. The data will be collected by an independent assessor who will be blinded to the study objectives and intervention. After completion of the study, a data entry officer will enter the data into the software. This will be checked/validated by another person by comparison with the original patient data file. Any mistakes made during data entry will be rectified at this point.

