**Methods/design:**

This is a randomized, single-blind, two-arm, controlled trial in patients with rheumatoid arthritis visiting outpatient rheumatology clinics in Karachi, Pakistan. We will enroll patients with established diagnosis of rheumatoid arthritis over 3 months. The patients would be randomized through a computer-generated list into the control group, i.e., usual care or into the intervention group, i.e., pharmaceutical care, in a ratio of 1:1, after providing signed written consent. The study will take place in two patient-visits over the course of 3 months. Patients in the intervention group would receive intervention from the pharmacist while those in the control group will receive usual care. Primary outcomes include change in mean score from baseline (week 0) and at follow up (week 12) in disease knowledge, adherence to medications and rehabilitation/physical therapy. The secondary outcomes include change in the mean direct cost of treatment, HRQoL and patient satisfaction with pharmacist counselling.

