### Study plan

The process will start after patients attend the study explanation session and consent to participate. The patients who refuse to participate will be provided regular hospital care. Patients who consent to participate will sign the patient consent form and will be screened for eligibility. Ineligible patients will be excluded from the study and given regular hospital care. Eligible patients will be randomized by computer software into the IG or CG. Patients’ baseline data will be recorded. Enrolled patients’ demographic data will be documented at baseline. Patients will have their anthropometric measurements, i.e., weight, height, etc. noted in addition to their socio-demographic data. Moreover, the patients will be assessed for the outcome measures. The patients randomized into the IG will be provided pharmacist intervention. At the follow-up appointment, i.e., after 3 months (week 12) from baseline (week 0), the same data will be recorded from patients in both treatment groups.

Attention is paid to achieving high patient-retention rates by comprehensively briefing the patients and answering their queries. In the case of loss to follow up, the rheumatologist and the hospital’s front desk staff will establish contact with the patient, try to convince them to participate and if not, document the reason for leaving the study. The whole study will encompass two visits in due course (Fig. 1).

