### Randomization and allocation concealment

Patients will be randomly allocated to one of the two treatment groups using a randomization ratio of 1:1. The technique used will be simple randomization using a computer-generated list. The participants’ medical record numbers will be entered into the hospital’s software and a list of appointments will be generated with patients designated into the CG or the IG.

Allocation will be automatically concealed through the computer-generated list, which automatically allocates a clinic room number. For instance, if the computer enrolls a patient into the IG, it generates the appointment slip with a clinic room number in which a pharmacist will provide the intervention and vice versa. There are two room numbers, i.e., 1 = without pharmacist intervention and 2 = with pharmacist intervention. The patients and data collectors will be unaware of this number scheme. Patients in the CG will go to clinic room 1 and have their consultation with rheumatologist. The pharmacist will not provide the intervention. Before consultation, the patients will go to a consultation room where a data collector will wait with a data file printed on yellow-colored paper. If the computer enrolls a patient into the IG, the appointment slip will be printed with clinic room number 2. Patients in the IG will go to that clinic room where the rheumatologist and a pharmacist await them. The patients will undergo the intervention after consultation with the rheumatologist. Similarly, before the intervention, patients will enter a consultation room where the data collector will wait with a patient data file printed on white paper. The data collector and pharmacist will be unaware of the color scheme. Therefore, the pharmacist will be unaware of outcome assessment.

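### Baseline questionnaires are taken after randomisation on arm-coloured forms, so masking of the baseline scores rests on a fixed two-colour, two-room code staying undeciphered

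*Protocol article*

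**What the plan says.** Two sections of the protocol article give the same order.

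- Study plan: "Eligible patients will be randomized by computer software into the IG or CG. Patients’ baseline data will be recorded".
- Data management: "The patients will be given a study explanation session and after giving their consent, will be randomized and have their baseline data documented".

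The section on randomization and allocation concealment adds the mechanics. The hospital software allocates the patient and prints a slip with a clinic room number: 1 without the pharmacist, 2 with. For an intervention patient, "the appointment slip will be printed with clinic room number 2". Before going to that room the patient meets a data collector. For control patients, "a data collector will wait with a data file printed on yellow-colored paper"; for intervention patients, "the data collector will wait with a patient data file printed on white paper".

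The protocol also states safeguards. The same section says that patients and data collectors do not know the room scheme, and that the data collector and pharmacist do not know the colour scheme. The Blinding section says that the data collector does not know the patient's group, and Table 1 marks data collectors and patients as not aware in every column. Data management describes an independent assessor blinded to objectives and intervention. Feasibility assessments has independent observers check the blinding.

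The Abstract and Discussion define the primary outcomes as changes in three mean scores from week 0 to week 12. Statistical analysis names a within-subject Wilcoxon signed-rank test as confirmatory.

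**The concern.** A baseline measured before allocation cannot be influenced by the arm. A baseline measured afterwards can be, if anyone who gives or takes the answers works out the arm. Here the arm is fixed before baseline and marked twice, on the patient's slip and on the collector's form.

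The code has two values, does not change, and ties each colour to one room. Linking a colour once to the room where the pharmacist sits would decode every later form. Even without decoding, the collector can see that patients fall into two groups.

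An arm-related shift in baseline enters the change score in full with the opposite sign, so it can look like an intervention effect or hide one. Two of the three primary scores (GMAS and GRAS) are adherence questionnaires, the kind of measure most open to such influence.

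**Working it through.** **Order of steps.** Study plan, Data management, and Randomization and allocation concealment agree: consent, allocation with a printed slip, baseline on a coloured form, then consultation, with the pharmacist session for the intervention arm. No section puts baseline before allocation. Baseline does precede the session, so the intervention itself cannot affect it; only knowledge or suspicion of the arm could.

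**What protects baseline.** Every stated safeguard is a form of not telling people what the code means. None removes the code from the slip or the form.

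**Routes to decoding.**

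- From what patients say at follow-up: the first enrolment was on 24 December 2018 (Trial status), so the first 12-week visit falls about 84 days later, on 18 March 2019. Recruitment was due to end on 31 March 2019. This route could reach only about the last 2 weeks of a roughly 14-week enrolment.
- From seeing which room holds the pharmacist: possible at any time, but the protocol does not say whether the collector can see this.

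**Illustration of size.** The protocol gives no figure for a baseline shift, so this part rests on assumptions.

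- Completers per arm: 619 × (1 − 0.20) / 2 = 247.6, from the total and drop-out rate in Sample size, taken as stated.
- Correlation ρ between baseline and week 12: assumed 0.5 to 0.7.
- No true effect; equal SDs; shift d in SD units; two-sided 5% test; normal approximation.
- SE of the between-arm difference in change = √(4(1 − ρ)/n). This is √(2/247.6) = 0.0899 at ρ = 0.5 and √(1.2/247.6) = 0.0696 at ρ = 0.7.
- False-positive rate = 1 − Φ(1.96 − d/SE) + Φ(−1.96 − d/SE).

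| Assumed shift d | ρ = 0.5 | ρ = 0.7 |
|---|---|---|
| 0 | 5% | 5% |
| 0.05 SD | 9% | 11% |
| 0.1 SD | 20% | 30% |

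At d = 0.1, d/SE is 1.11 and 1.44. With baseline adjustment instead (bias ρd, SE = √(2(1 − ρ²)/n)), the rates at 0.1 SD are about 10% and 19%.

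The protocol names neither of these tests. For the within-subject test that it does name, a paired normal approximation with the whole 0.1 SD falling in one arm has SE = √(2(1 − ρ)/n) = 0.0636 and 0.0492. That gives about 35% and 53% in that arm.

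**The case against.** The strongest reply is that the protocol declares the codes undisclosed and the assessor blinded, even to the study objectives. A collector who sees two colours still does not know which is which, and would have no evident reason to push one of them in a given direction. This stands.

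A reader might infer that staff or patients know the allocation at baseline, or that the colours become obvious after a few patients. The documents support neither. They state the opposite for patients and collectors, and they do not say that the collector sees who is in the next room. Nor do they say that the questionnaires are given by interview. The knowledge score (RAKAS) is a multiple-choice test marked right or wrong, which leaves less room for influence.

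The error rates are also open to challenge. The shifts are assumed, and the between-group comparisons in Statistical analysis are made at a single time point. A comparison at week 12 alone is untouched by a baseline shift. So the figures are illustrations, not estimates.

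What remains is that the declared masking relies on secrecy alone, and the account of it is not fully consistent. Table 1 lists pharmacists and rheumatologists as unaware of the intervention room, although they sit in it. The Blinding text says that study observers are blinded to allocation, while Table 1 lists them as aware of the allocation scheme and the colour code.

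**Conclusion.** The point holds as a design weakness: an avoidable risk of unmasking at baseline, not shown knowledge of allocation and not shown bias. The order of steps and the arm-coloured forms are explicit in the text, and baseline enters all three primary change scores and the confirmatory within-subject test.

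The size is unknown. If a 0.1 SD shift between arms did occur, a between-arm change-score test would reject falsely about 20% to 30% of the time, given about 248 completers per arm and a correlation of 0.5 to 0.7. With no shift the rate is 5%. The document gives no evidence that any such shift arises.

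Loss of patients between allocation and baseline is a minor addition. The two steps appear to fall at the same visit, and no such loss is reported.

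**What to change.** In Study plan, Randomization and allocation concealment, and Data management, set the order as consent, eligibility, baseline questionnaires, and only then running the allocation software and printing the slip. Use one identical uncoloured form in both arms at both visits; the arm can be linked later through the medical record number.

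The cost is a small change to the workflow of the appointment software, which now generates the list with arms already assigned. No visits or staff are added.

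Trial status says that the trial is no longer recruiting and that results are being analysed, so the order cannot be changed for this trial. The report should instead state that baseline followed allocation on coloured forms, show baseline scores by arm, and give the number randomised in each arm who have no baseline.

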### Statistical analysis

The statistical analysis will be conducted by a statistician who will be blinded to patient-group allocation. The analysis will be carried out using SPSS version 22 (IBM SPSS, Armonk, NY, USA). The analysis will consist of a per-protocol set that includes participants who have completed the study as per the defined protocol. The significance level will be set at 5% and a two-tailed test will be used. Continuous data will be descriptively analysed using the Mann-Whitney U test, while the chi-square test will be used to analyze categorical variables by comparing them in the two groups at the same time point. Confirmatory analysis will be carried out using the Wilcoxon signed-rank test to analyze differences in the mean values for disease knowledge, adherence to treatment and medications and the cost of treatment after 3 months, i.e., baseline within-subject analysis. Multinomial logistic regression will be used to interpret the odds ratios for the secondary outcome, i.e., patient satisfaction with pharmacist counselling. There will be no interim data analysis.

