### Objectives

The primary objective of the study is to evaluate the effectiveness of a multifactorial educational intervention on patient knowledge of RA and adherence to treatment. This intervention would be provided by a pharmacist. The secondary objectives are to assess the impact of the intervention on the cost of treatment, quality of life and patient satisfaction.

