### Trial design

This trial is designed as a randomized, single-blind, parallel group trial. It has two arms, i.e., a control or “usual care” arm and an intervention or “pharmaceutical care” arm. Patients would be recruited and randomly assigned to either of the two arms using a computer-generated list and the patients’ medical record numbers. The allocation ratio would be 1:1. The trial has been designed as per the Standard Protocol Items: Recommendations for Interventional Trials (SPIRIT) and Template for Intervention, Description and Replication (TIDieR) checklists which are available as Additional files 1 and 2.

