### Sample size

Few randomized controlled trials have evaluated the effect of pharmacists’ educational interventions on adherence and disease knowledge among patients with RA. We reviewed several studies that could serve as a reference for calculation of sample size based on treatment effect. A study conducted by Clifford and colleagues assessed the effect of pharmacist educational advice on improving adherence [7]. Another study by Stockl and colleagues was nonrandomized and was limited to evaluating the effects of a telephone intervention by either a pharmacist or a nurse, on patients’ adherence to injectable RA medicines [8]. Azzopardi and colleagues used a different outcome measure to ours and included patients with RA prescribed methotrexate only [28]. Similarly, in another RCT, Petkova measured a different outcome [3].

We considered a study by Clifford and colleagues as a standard and calculated our sample size based on the primary outcome, i.e., adherence [7, 29]. It was taken as a reduction in self-reported nonadherence from 16% to 9% considering a (two-side) alpha value of 0.05 and statistical power of 80%, i.e., beta = 0.2. Considering a drop-out rate of 20%, we would require a total of 619 patients to successfully demonstrate a positive and statistically significant effect.

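### Per-protocol completers are the only stated analysis set in an effectiveness trial with adherence as a primary outcome, so the comparison loses the protection of randomisation and can be biased in either direction

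*Protocol article*

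**What the plan says.** The Objectives section puts an effectiveness question: "The primary objective of the study is to evaluate the effectiveness of a multifactorial educational intervention on patient knowledge of RA and adherence to treatment". The Outcomes section makes medication adherence and rehabilitation adherence primary outcomes, together with disease knowledge, each assessed at baseline and week 12.

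The Statistical analysis section then names the population: "The analysis will consist of a per-protocol set that includes participants who have completed the study as per the defined protocol". The article names no other set, no method for missing outcomes and no sensitivity analysis.

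The Sample size section expects losses: "Considering a drop-out rate of 20%, we would require a total of 619 patients". For patients lost to follow-up, the Study plan section provides for renewed contact and a record of the reason. It has no rule for keeping them in the analysis.

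**The concern.** A trial of whether offering pharmacist care improves adherence and knowledge is a superiority comparison of two randomised groups. It is protected against confounding only if patients are analysed in the groups to which they were allocated. Restricting the analysis to completers selects patients on something that happens after allocation.

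Two features of this trial sharpen the point. First, completing means coming back at week 12, and failing to come back is plausibly related to poor adherence, which is the outcome itself. Second, only the intervention arm has a counselling session to receive, and the Blinding section says that patients are not blinded to the pharmacists. Completion according to protocol could therefore select differently in the two arms.

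This is a population that the article positively fixes, and it governs every outcome. It is not a detail left open for a separate analysis plan. At stake is whether a between-arm difference can be attributed to the intervention at all.

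**Working it through.** **Inputs from the article**
- Planned total 619, including 20% drop-out (Sample size). No split by arm is given.
- Allocation: "The allocation ratio would be 1:1" (Trial design), so on average 619/2 = 309.5 per arm.
- Planning rates of non-adherence: 16% against 9%, a difference of 7 points (Sample size).

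**Assumed, because the article gives nothing:** drop-out in each arm, and the share q of drop-outs who are non-adherent.

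**The plan's own figure.** With two-sided 5% significance, 80% power and 16% against 9%, the usual pooled formula gives 350 per arm, or 700 in total, and 700/0.80 = 875 after drop-out. The figure of 619 is not reproduced. That is a separate matter; here 619 serves only as the number to be randomised.

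**Patients affected.** 619 × 0.20 = 123.8, about 124, leaving about 495.

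**Size of a possible bias with no true effect.** Let true non-adherence be 16% in both arms and drop-out 20% in both. In an arm whose drop-outs have non-adherence q, the rate seen among completers is

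(0.16 − 0.20 × q) / 0.80

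| q in one arm only (other arm 16%) | Completers in that arm | Spurious difference in favour of that arm | Share of the 7-point planning effect |
|---|---|---|---|
| 16% | (0.16 − 0.032)/0.80 = 16.0% | 0 | 0% |
| 25% | (0.16 − 0.050)/0.80 = 13.75% | 2.25 points (about 2.3) | 32% |
| 30% | (0.16 − 0.060)/0.80 = 12.5% | 3.5 points | 50% |
| 40% | (0.16 − 0.080)/0.80 = 10.0% | 6.0 points | 86% |

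**Sign.** If the arm concerned is the intervention arm, the bias favours the intervention. If it is the control arm, the same number counts against it. If q is the same in both arms, the difference is zero, although both completer rates then fall below 16% when q exceeds 16%.

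**False-positive rate.** Suppose that in one arm only, non-adherent patients are twice as likely to drop out. Drop-out is then 0.20/(0.84 + 2 × 0.16) = 17.2% in adherent and 34.5% in non-adherent patients. Completers show 0.16 × (1 − 0.345)/0.80 = 13.1% against 16.0%, a difference of 2.9 points. With 309.5 × 0.80 = 247.6 completers per arm, a two-sided 5% test of two proportions rejects in about 15% of trials. At three times as likely, the difference is 5.1 points and the rejection rate about 38%.

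**Unequal drop-out.** With 15% drop-out in control, 25% in intervention, and non-adherent patients twice as likely to leave in both arms, completers show 14.0% and 12.1%. That is 1.8 points in favour of the intervention, with a rejection rate of about 9%. With the drop-out rates exchanged, it is 1.8 points against.

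**The case against.** The strongest reply is that no bias has been shown. Bias in the comparison needs drop-out that is related to outcome and also differs between arms, and the article gives data on neither. The main hurdle to completion, the week-12 visit, is the same in both arms, with the same text and telephone reminders and the same re-contact of absentees. The session is a single contact of 20–25 minutes following the rheumatologist's consultation, so few patients may miss it, and the article does not say outright that receiving it defines the set. All this stands, and it limits what can be claimed.

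A reader might infer three stronger things:
- **That the set biases the result toward the intervention.** This is plausible, but the reversed pattern fits the article equally well.
- **That non-adherence is understated.** This holds only if drop-outs are less adherent than completers, which the article does not say.
- **That the per-protocol rule itself costs about 124 patients.** The 20% is a planning allowance. With one follow-up visit, drop-outs have no week-12 score under any analysis set. What the rule alone removes is patients who have a week-12 score but deviated from protocol; their number is unknown and may be small.

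Two further objections bear on the remedy. Multiple imputation assumes missingness at random given the variables used; if baseline data do not explain why drop-outs do worse, the illustrated bias partly remains. Also, the article attaches the word confirmatory to a within-patient signed-rank test. A change of analysis set protects only a between-arm comparison; the choice of test is a separate question.

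None of this defends the sole use of a completer set. It shows that the direction of bias is unknown and that the fix must do more than impute.

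**Conclusion.** The point holds in this form. The only stated analysis set selects patients on a post-randomisation event plausibly related to a primary outcome, in an effectiveness trial that expects one patient in five to be lost. The comparison is then no longer protected by randomisation, and readers could not tell which drop-out pattern had occurred.

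The possible size is material: under the assumed one-arm patterns, about a third to six-sevenths of the planning effect. The direction is open, and zero is possible. The figures rest on assumed drop-out behaviour and on a binary adherence rate taken from the Sample size section. The primary outcomes are changes in mean scores, so the figures show scale and are not a forecast. The conclusion does not depend on whether 619 can be reproduced. Because the rule governs every primary comparison, it should be changed before the results are relied on.

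**What to change.** - **Primary set:** all randomised patients in their assigned arm, whether or not the session was received, including every available week-12 score.
- **Missing week-12 scores:** multiple imputation from arm, baseline score, hospital and baseline covariates, with a sensitivity analysis for departures from missing at random in which the assumption is allowed to differ by arm.
- **Per-protocol set:** keep it as a sensitivity analysis.
- **Reporting:** drop-out and its documented reasons by arm.
- **Amendment:** the Trial status section says that the final results are being analysed, so the change needs a dated, disclosed amendment that states whether data had been seen.

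The cost is an imputation step, the amendment, and an estimate that may be less favourable. No new data are needed: baseline data are recorded in both arms, and the reasons for leaving are already to be documented.

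### The confirmatory test compares patients with their own baseline, so the randomised comparison between arms does not decide whether the intervention works

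*Protocol article*

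**What the plan says.** The Statistical analysis section gives each test a role.

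- **Confirmatory.** "Confirmatory analysis will be carried out using the Wilcoxon signed-rank test to analyze differences in the mean values for disease knowledge". The sentence goes on to adherence and ends with "the cost of treatment after 3 months, i.e., baseline within-subject analysis". The comparison is thus week 0 against week 12 in the same patient.
- **Between arms, continuous data.** "Continuous data will be descriptively analysed using the Mann-Whitney U test".
- **Between arms, categorical data.** "the chi-square test will be used to analyze categorical variables by comparing them in the two groups at the same time point". This test carries neither label.
- **Level and analysis set.** "The significance level will be set at 5% and a two-tailed test will be used", applied to patients who completed the study per protocol.

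The Objectives section sets the primary aim: to "evaluate the effectiveness of a multifactorial educational intervention on patient knowledge of RA and adherence to treatment". The Trial design section describes two randomised parallel arms allocated 1:1. The Abstract and Discussion define the primary outcomes as changes in mean score for knowledge, medication adherence and rehabilitation adherence. No other section names a confirmatory between-arm test. The mixed model in the Intervention section serves to observe implementation by pharmacist, not to estimate the treatment effect.

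**The concern.** Whether the intervention works is a question about the difference between arms. A signed-rank test on paired values asks instead whether scores moved over 12 weeks in the patients tested, and the control group plays no part in the answer.

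Scores can move for reasons that both arms share: a second attempt at the same 13-item multiple-choice knowledge test, awareness of being in a study, the rheumatologist's consultation, disease course and regression to the mean. Randomisation to usual care is there to remove these, and a within-patient test puts them back.

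Running the test in each arm and comparing the two p-values does not repair this, because significance in one arm and not in the other is not a test of the difference between them. As written, the trial could report a confirmatory positive result when both arms improved equally.

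**Working it through.** **1. Is there a figure to reproduce?** The plan gives none for this analysis. The only number borrowed is the sample size: 619 patients with 20% drop-out (Sample size section) leaves 619 × 0.8 / 2 = 247.6, taken as 247 completers per arm. The 619 does not itself follow from its stated inputs: 16% against 9%, two-sided 5% and 80% power give 350 per arm, 700 evaluable and 700 / 0.8 = 875 with drop-out. That is a separate matter, and nothing below depends on it except the choice of n.

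**2. Assumptions.** The documents give no SD, no correlation between baseline and follow-up, and no expected change under usual care. Assume:
- normal change scores with SD 1;
- the same mean drift δ (in SD of change) in both arms, so no treatment effect;
- each test two-sided at 5%.

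With correlation r = 0.5 and unit SD at each visit, the variance of change is 2 × (1 − 0.5) = 1, so one SD of change equals one SD of the score.

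**3. Rejection rate of the within-arm test.** For normal data the signed-rank test has efficiency 3/π = 0.955 relative to the paired t-test, so approximately

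p(δ) = Φ(δ√(0.955n) − 1.96) + Φ(−δ√(0.955n) − 1.96).

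With n = 247, √(0.955 × 247) = 15.36. At δ = 0.1 this gives Φ(1.536 − 1.96) = Φ(−0.424) ≈ 0.34. At δ = 0.2 it gives Φ(3.072 − 1.96) = Φ(1.112) ≈ 0.87.

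**4. Reading the two arms side by side.** With no treatment effect the arms are independent and have the same p, so the chance of a significant result in the intervention group (IG) but not the control group (CG) is p(1 − p). At δ = 0.1 this is 0.336 × 0.664 = 0.22.

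**5. Results.** The first two result columns are from the formulas. The third is from 2,000 simulated trials per row, run for four of the drifts. The same simulations agree with the formulas to within about 0.01.

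| Common drift δ | IG signed-rank significant | IG significant, CG not | Between-arm Mann-Whitney on change |
|---|---|---|---|
| 0 | 5% | 5% | 5.9% |
| 0.05 | 12% | 11% | – |
| 0.10 | 34% | 22% | 4.9% |
| 0.15 | 63% | 23% | – |
| 0.20 | 87% | 12% | 4.6% |
| 0.30 | 99.6% | 0.4% | 5.1% |

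The side-by-side reading errs most at drifts of 0.10 to 0.15. Its error falls at larger drifts only because both arms then become significant.

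**6. If the arms are pooled.** The text does not say whether the test is run per arm. Pooled, n = 494 and √(0.955 × 494) = 21.72, so at δ = 0.1 the rate is Φ(2.172 − 1.96) = Φ(0.212) ≈ 0.58, and the result says nothing about the intervention.

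**7. Gain from baseline adjustment.** The difference detectable with 80% power, unadjusted, is 2.80 × √(2/247.5) = 0.252 SD. Adjusting for baseline at an assumed r = 0.5 multiplies it by √(1 − 0.25) = 0.866, giving 0.218 SD.

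**The case against.** Between-arm tests are planned, and the word descriptive is attached only to the Mann-Whitney test. The chi-square test is free of that label, and it suits the contrast used for the sample size, which is a proportion. The section also states no success rule, so both the IG-only reading and the side-by-side reading are supplied by the reader. The drift sizes and r are assumed. The shared reminders are weak evidence of drift: "they are reminded about their visits via text reminders and followed by telephone calls if absent" describes prompts for appointments, not for medication or exercise. Finally, an unadjusted between-arm comparison is valid under randomisation, so baseline adjustment is a preference.

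Most of this stands as qualification. The chi-square test should not be called descriptive, the argument does not need the reminders, and ANCOVA is one valid choice among several. None of it moves the confirmatory label. The chi-square test is not called confirmatory and does not analyse changes in mean score, which are the stated primary outcomes. The missing success rule does not help either, since no way of running a within-patient test alone compares the arms. Nor can the matter be left to a separate analysis plan, because the article itself fixes which test confirms.

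**Conclusion.** The concern holds and must be fixed. The article gives the confirmatory role to a test that cannot answer the primary objective. If both arms drift equally by 0.1 to 0.2 SD of change, the IG test is significant in about 34% to 87% of trials with no treatment effect, against about 5% for a between-arm test on change. These rates rest on normal change scores, 247 completers per arm and the assumed drifts. The 22% to 23% false-positive rate for the side-by-side reading applies only if the results are read that way. At exactly zero drift the within-arm test keeps its 5% level, but nothing in the document supports assuming zero. The loss of precision from not adjusting for baseline (0.25 against 0.22 SD) is secondary.

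**What to change.** Rewrite the analysis paragraph so that the confirmatory analysis of each primary score (RAKAS, GMAS, GRAS) is the difference between arms at week 12, with a 95% confidence interval. ANCOVA with baseline score as covariate is the natural choice, and hospital can be added because there are three sites. Mann-Whitney on change from baseline can serve as a sensitivity analysis, and would also be acceptable as the confirmatory test. Keep the within-arm signed-rank tests as description only. Use the same between-arm approach for cost, which the present wording includes in the within-patient analysis, and for HRQoL. Since three scores would be confirmatory, state how success across them is judged.

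No new data are needed: both arms are measured at week 0 and week 12, and each outcome needs one standard model in SPSS. The real cost is timing. The Trial status section says the final results are being analysed, so the change should be dated and disclosed as such, with a statement that the statistician was still blinded to allocation when it was made.
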